#### 2.2.5 Sample size estimation

This is a pilot study aimed at preliminarily evaluating the effect of GQHF combined with Ixekizumab for PV on relapse reduction. Notably, there is a lack of relevant studies providing basic data for sample size calculation of this study. Additionally, published research (Sim and Lewis, 2012) recommends enrolling at least 50 participants in a dual-arm pilot randomized controlled trial when there is high confidence. Therefore, this study aims to enroll 50 participants for preliminary assessment.

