#### 2.2.8 Outcomes

##### 2.2.8.1 Primary outcome

Rate of relapse is the primary outcome, wherein relapse is defined as the loss of response of at least 75% improvement in PASI score from baseline (PASI-75) during the follow-up period by participants who achieve PASI-75 after treatment (Warren et al., 2021; Mrowietz et al., 2015).

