##### 2.2.8.2 Secondary outcomes

(1) Time to relapse, defined as the interval between the completion of the last treatment and the occurrence of disease relapse.(2) Improvement in PASI score from baseline.(3) Proportion of participants achieving PASI-75.(4) Proportion of participants achieving at least 90% improvement in PASI score from baseline (PASI-90).(5) Changes in PGA score.(6) Changes in VAS score.(7) Changes in Dermatology Life Quality Index (DLQI) score.(8) Changes in Skindex16 score.

PASI-75, PASI-90, BSA and PGA are the recommended outcome measures for assessing the efficacy of PV (Elmets et al., 2021; Committee on Psoriasis, 2023). Regarding the assessment of quality of life, the DLQI is a validated and recognized measure involving aspects of symptoms, feelings, daily activities, recreation, work, study, personal relationships and therapy (Atwan et al., 2017; Mermin et al., 2016). Additionally, the Skindex 16 is another assessment scale that has been proven sensitive and highly applicable in the treatment of PV (Hopkins et al., 2023; He et al., 2014).

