#### 2.2.11 Statistical analysis

Statistical analyses will be conducted utilizing PASW Statistics 26.0 (IBM SPSS Inc, Armonk, New York, USA) and R statistical software version 4.4.1 by an independent statistician blinded to group allocation. Missing data will be involved with the last observation carried forward (LOCF) method. The primary analysis will be focus on the intention-to-treat (ITT) population, including all randomized subjects. Concerning efficacy analysis, frequency counts and percentages of participants in each arm will be calculated for categorical data (such as relapse rate), and group comparisons will be conducted using chi-squared test or Fishers exact test appropriately. Continuous variables will be presented as means with standard deviations for normally distributed data, or medians with interquartile ranges for non-normally distributed data. Group comparisons will be conducted by the t-test or Wilcoxon rank-sum test. For rank data (such as PGA score), intergroup comparison will be performed using the Wilcoxon rank sum test or Cochran-Mantel-Haenszel test. For repeated measures analysis, generalized estimating equations (GEE) or Cumulative Link Mixed Model (CLMM) will be employed to evaluate data across all follow-up time points. The Log-rank test will be utilized to compare the “time to relapse” and “time to achieve improvement” between two groups. All statistical tests will be conducted using a two-tailed hypothesis, with *p* values ≤0.05 considered indicative of statistical significance.

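### Relapse is defined only for PASI-75 responders but analysed in all randomised participants, so a lower response rate can read as less relapse

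*Protocol article*

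**What the plan says.** Section 2.2.8.1 makes the relapse rate the primary outcome. Relapse is loss of PASI-75 "during the follow-up period by participants who achieve PASI-75 after treatment", so a participant who never reaches PASI-75 cannot have the event.

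Section 2.2.11 sets the population: "The primary analysis will be focus on the intention-to-treat (ITT) population, including all randomized subjects". On the summary it says that "frequency counts and percentages of participants in each arm will be calculated for categorical data (such as relapse rate" is the example given, and that "group comparisons will be conducted using chi-squared test or Fishers exact test appropriately". Significance is judged at the two-sided 5% level.

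On missing values the same section says: "Missing data will be involved with the last observation carried forward (LOCF) method". It gives no rule for participants who are observed and do not respond.

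The PASI-75 proportion is a separate secondary outcome in section 2.2.8.2. Time to relapse, also secondary, is "defined as the interval between the completion of the last treatment and the occurrence of disease relapse", and so has the same set of people at risk. No section names a responder analysis set or says how non-responders are scored for relapse.

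**The concern.** The endpoint definition points to one denominator (responders) and the analysis section to another (everyone randomised). Each reading has its own problem.

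- **All randomised.** Non-responders count as not relapsed. So does anyone who leaves during treatment before reaching PASI-75, because LOCF carries that person forward as a non-responder. Failing to respond is then scored the same way as responding and staying clear, and an arm can lower its relapse rate by having fewer responders.
- **Responders only.** Section 2.2.7 gives GQHF or placebo over the same 12 weeks as ixekizumab, so the granule may influence who becomes a responder. The two groups being compared are then selected on a post-randomisation outcome.

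At stake is the headline result of the trial, and the preliminary relapse figures that section 3 intends to use for a larger study.

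**Working it through.** **Nothing to reproduce.** The total of 50 in section 2.2.5 comes from a published minimum for two-arm pilot trials. No relapse rate, effect or power lies behind it.

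**Inputs from the article**
- 50 participants allocated 1:1, so 25 per arm (2.2.5, 2.2.6).
- Follow-up of 36 weeks (2.2.7).
- Median time to relapse after ixekizumab of about 20.4 weeks (section 3).
- Chi-squared or Fisher's exact test, two-sided, p ≤ 0.05 (2.2.11).

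**Assumptions, not in the article**
- Relapse times are exponential.
- Relapse risk among responders is the same in both arms, so GQHF has no effect on durability.
- PASI-75 rates range from 60% to 90%.

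**Step 1. Relapse among responders by 36 weeks**

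q = 1 − 0.5^(36/20.4) = 1 − 0.294 = 0.706

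**Step 2. Relapse rate with all randomised participants in the denominator**

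Rate = P(PASI-75) × q

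The last column is the exact probability of a significant result favouring the intervention with 25 per arm, given as Fisher / uncorrected chi-squared.

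| PASI-75 control / intervention | Relapse control | Relapse intervention | Apparent advantage of intervention | P(significant for intervention) |
|---|---|---|---|---|
| 90% / 90% | 63.5% | 63.5% | 0 | 1.4% / 2.9% |
| 90% / 80% | 63.5% | 56.5% | 7.1 points | 4.8% / 8.5% |
| 90% / 70% | 63.5% | 49.4% | 14.1 points | 12.6% / 19.7% |
| 90% / 60% | 63.5% | 42.3% | 21.2 points | 26.3% / 36.7% |
| 80% / 90% | 56.5% | 63.5% | −7.1 points | 0.4% / 0.8% |

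In the last row the intervention responds better and looks worse. The probability of a significant result for control there is 4.8% / 8.5%.

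**Step 3. Sensitivity to q**

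A 10-point PASI-75 difference shifts the rate by 10 × q points. That is 5 points at q = 50% and 9 points at q = 90%.

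**Step 4. The alternatives, at PASI-75 of 90% control and 80% intervention**
- Responders only: 70.6% against 70.6%. There is no difference here because q was set equal, but the groups are no longer those that were randomised.
- Failure defined as no PASI-75 or relapse, in all randomised: 1 − 0.90 × 0.294 = 73.5% against 1 − 0.80 × 0.294 = 76.5%. The direction reverses, and the arm with fewer responders now looks slightly worse, as it should.

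**The case against.** Several points on the other side have weight.

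1. **The coding is inferred.** A reader might take it that the protocol scores non-responders as relapse-free. It never says so. That follows only from joining the endpoint definition to the analysis population. The ITT sentence is general, and the definition could be read as making responders the denominator. This stands. The article is also condensed, and a fuller plan might settle the matter. Even so, the text shown does not merely stay silent: it fixes a population that does not match its endpoint.
2. **The all-randomised comparison is not biased.** A reader might infer that both readings lose the protection of randomisation. Only the responder reading does. The all-randomised one validly compares the probability of responding and then relapsing. Its fault is that this quantity is misleading as a measure of benefit. This stands.
3. **No tilt towards GQHF is shown.** A reader might infer a built-in advantage for the combination. Both arms receive the same ixekizumab schedule, nothing in the article suggests that GQHF lowers response, and its rationale points the other way. If GQHF raises response, the distortion works against it. This stands.
4. **The clock for time to relapse.** A reader might also object that it starts after randomisation. That is not a separate fault. For participants who complete treatment its start nominally coincides with week 12, and any clock for relapse after treatment must start after randomisation.
5. **It is a small pilot, and PASI-75 is reported separately.** The aim is modest ("Therefore, this study aims to enroll 50 participants for preliminary assessment"), and an imbalance in response would be visible among the secondary outcomes. That softens the problem without resolving it. Relapse rate is still the primary endpoint, and the article still says: "All statistical tests will be conducted using a two-tailed hypothesis, with *p* values ≤0.05 considered indicative of statistical significance".

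**Conclusion.** The concern holds in this form: the primary outcome and the primary analysis population do not fit each other, and the literal combination gives a relapse rate that falls when response falls. The size is conditional. With about 70% of responders relapsing in both arms, each 10 points of PASI-75 deficit yields about 7 points of spurious advantage, and each 10 points of PASI-75 gain costs the better arm the same. With equal response the rate is diluted but does not favour either arm.

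These figures rest on an exponential reading of the 20.4-week median and on assumed PASI-75 rates. With 25 per arm and a 10-point gap, false significance is a minor risk (4.8% by Fisher's test, 8.5% by chi-squared). The larger risk is a misleading point estimate carried into the next trial.

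**What to change.** Before unblinding, amend sections 2.2.8.1 and 2.2.11 and the registry entry, with the date and reason for the change.

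- **Primary analysis, all randomised participants:** the proportion with PASI-75 at the end of treatment who keep it through the 36-week follow-up. Non-response and relapse both count as failures.
- **Alongside it:** relapse rate and time to relapse among end-of-treatment PASI-75 responders, with that denominator stated and the comparison labelled as one within a post-randomisation subgroup.

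The composite is not the only defensible choice. At the least, the denominator and the scoring of non-responders must be stated.

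The cost is small, since the PASI data are already collected. There are two drawbacks. The composite mixes initial response with durability, which the responder analysis separates again. The headline endpoint also changes late, with recruitment due to end in January 2025, so the change must be documented as made blind.

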### 2.2 Quantitative study (A randomized controlled trial)

#### 2.2.1 Study setting

The randomized controlled trial will be conducted at Guangdong Provincial Hospital of Chinese Medicine in Guangzhou, China. All participants will be recruited from public or dermatology outpatient departments.

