#### 2.2.6 Randomization and blinding

Recruited participants will be randomly allocated to the intervention group and the control group in a 1:1 ratio. Computer-generated random list and permuted block size for center-stratified method are generated with SAS 9.2 software. Participants and researchers will be rigorously blinded to the group allocation. According to the blinding requirement of study, the granule of GQHF and GQHF placebo will be packaged and labeled identically with randomized codes by an independent researcher. The blinding codes are generated after randomization. Blinding will be maintained until data validation and editing are complete, or in the onset of serious adverse events.

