However, there are also several limitations needed to be addressed. Firstly, patients older than 70 years old and younger than 18 years of age are excluded in this study, since it is unclear whether the combined treatment of GQHF and Ixekizumab is suitable for these age groups. Additionally, due to the absence of relevant published studies on the application of GQHF combined with Ixekizumab, the sample size calculation of this pilot study is based on the minimum sample size of dual-arm pilot trials (Sim and Lewis, 2012), which may affect the generalizability and reliability of the findings. Therefore, after completing this pilot study, we intend to conduct the next phase study with a larger sample size and multiple research centers as planned.

In summary, this pilot study aims to evaluate the feasibility and acceptability of combing GQHF with Ixekizumab to reduce PV relapse. To comprehensively investigate the effect of GQHF combined with Ixekizumab for PV, study design of MRR is utilized, containing a randomized controlled trial for feasibility assessment and a semi-structured interview for acceptability evaluation. The findings of this study may indicate a novel therapeutic option for PV in reducing relapse and provide preliminary data for further MMR study with larger sample and multiple centers.

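### Continuous secondary outcomes are compared by tests that do not adjust for the baseline score: valid, but less precise than ANCOVA on data already collected

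*Protocol article*

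**What the plan says.** Section 2.2.11 (Statistical analysis) describes how continuous variables are summarised and then states: "Group comparisons will be conducted by the t-test or Wilcoxon rank-sum test". It names no baseline covariate for these comparisons. The same section plans GEE or a cumulative link mixed model for repeated measures, also without listing covariates. The relapse rate is compared by a chi-squared or Fisher test.

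The continuous outcomes are in Section 2.2.8.2: PASI improvement from baseline, and changes in VAS, DLQI and Skindex-16. Section 2.2.4 lists PASI and VAS among the enrolment assessments. Section 2.2.10 has data collected at baseline, and a change in DLQI or Skindex-16 cannot be formed without a starting value.

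On size, Section 2.2.5 says: "Therefore, this study aims to enroll 50 participants for preliminary assessment". Section 2.2.6 has these "randomly allocated to the intervention group and the control group in a 1:1 ratio".

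Section 2.2.6 also says that a random list and "permuted block size for center-stratified method are generated with SAS 9.2 software". Section 2.2.1 names one site: "The randomized controlled trial will be conducted at Guangdong Provincial Hospital of Chinese Medicine in Guangzhou, China". The Discussion places several centres in a later study: "we intend to conduct the next phase study with a larger sample size and multiple research centers as planned".

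**The concern.** A t-test on a change score subtracts the whole baseline value, whatever the correlation between baseline and follow-up. When that correlation is modest, the subtraction adds noise. ANCOVA estimates how much of the baseline to remove. It targets the same treatment contrast, usually with a smaller variance, and it also takes out the part of a chance baseline difference that carries through to the outcome.

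In a pilot of 50 the estimates and their intervals are the main product, and the Discussion says that they are meant to inform a larger trial. Precision given up in the analysis comes on top of a sample size that the Discussion already lists as a limit on reliability. The baseline values are in hand, so the loss is avoidable.

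**Working it through.** **1. Sample size.** 50 participants at 1:1 is 50/2 = 25 per arm. The 50 comes from a published pilot-trial minimum (Section 2.2.5), not from a power calculation, so there is no power figure to reproduce.

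**2. Assumptions.** The article gives no SD and no correlation. Let r be the correlation between baseline and follow-up (assumed 0.3, 0.5, 0.7), and take equal SDs at the two times. Variances are relative to that of a raw follow-up score.

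- t-test on change: 2(1 − r)
- ANCOVA with one covariate: (1 − r²) × (1 + 1/46), where 46 = 2 × 25 − 4 is the small-sample cost of estimating the slope

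| r | Change score | ANCOVA | Ratio | Change-score n per arm with ANCOVA's precision at 25 |
|---|---|---|---|---|
| 0.3 | 1.40 | 0.91 × 1.0217 = 0.930 | 0.66 | 25/0.664 = 37.6 |
| 0.5 | 1.00 | 0.75 × 1.0217 = 0.766 | 0.77 | 25/0.766 = 32.6 |
| 0.7 | 0.60 | 0.51 × 1.0217 = 0.521 | 0.87 | 25/0.868 = 28.8 |

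Without the small-sample factor the ratio is (1 + r)/2 = 0.65, 0.75, 0.85.

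**3. Interval width.** The 95% half-width in SD units is 1.96 × √(variance × 2/25).

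- Change score: 0.656, 0.554, 0.429
- ANCOVA: 0.535, 0.485, 0.400
- Reduction: about 18%, 12% and 7%

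**4. Power, for illustration.** For an assumed difference of 0.8 SD, two-sided 0.05, the normal formula gives 67%, 81% and 96% for the change score and 84%, 90% and 98% for ANCOVA. Simulation (4,000 trials per setting) gave 80% against 88% at r = 0.5 and 95% against 97% at r = 0.7.

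**5. Unequal SDs.** Let k be the follow-up SD divided by the baseline SD. In baseline-variance units the change score has 1 + k² − 2rk and ANCOVA, before the small-sample factor, has k²(1 − r²). The difference is (1 − rk)², which is never negative. At k = 0.5 the ratios are 0.2275/0.95 = 0.24, 0.1875/0.75 = 0.25 and 0.1275/0.55 = 0.23. The least favourable case is rk = 1, where ANCOVA costs only the factor 1.022.

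**6. Chance imbalance.** The standardised baseline difference between arms has SD √(2/25) = 0.28. An absolute difference above 0.3 SD has probability about 29%, and above 0.5 SD about 8%, for each score.

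**7. Primary outcome.** With a median time to relapse of 20.4 weeks (Discussion), and assuming an exponential curve, 1 − 2^(−36/20.4) = 71% would relapse by the end of the 36-week follow-up. Taking 70% against an assumed 40% at 25 per arm, simulation (1,500 trials per setting) gave power of about 61–64% for chi-squared and 49–51% for Fisher. Logistic regression with one baseline covariate gave 59%, 61%, 62% and 67% for assumed prognostic odds ratios of 1.0, 1.5, 2.0 and 3.0 per SD. Adjustment gives a clear gain over chi-squared only at 3.0.

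**The case against.** The strongest reply is that nothing is wrong with the stated tests. Under 1:1 randomisation the unadjusted comparisons are valid, and their standard errors already allow for chance imbalance. That stands: this is a matter of efficiency, not of type I error. It is also fair that the trial is a pilot with no power or precision target, that "there is a lack of relevant studies providing basic data for sample size calculation of this study", and that the correlations and SDs above are assumed. The formula covers absolute change analysed by a t-test. It does not cover the rank-sum alternative, or percentage improvement in PASI, which Section 2.2.8.2 leaves open.

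Four stronger readings are tempting, but the documents do not support them.

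- **Baseline scores go unused.** They form the change scores (Section 2.2.8.2) and the PASI-75 definition on which relapse rests (Section 2.2.8.1). What is absent is their use as covariates in the named tests.
- **No analysis is adjusted.** GEE and CLMM can carry baseline terms, and an analysis plan that is not shown may list them. Their absence from an article is not a fault. The t-test and rank-sum test, however, are a stated choice that ANCOVA would replace.
- **The primary test should be replaced.** Step 7 shows little or no gain unless baseline is strongly prognostic, and nothing in the article says that baseline PASI predicts loss of response. Relapse is defined among those who reach PASI-75, so such a model might also run on fewer than 25 per arm.
- **The centre stratum causes the loss.** Stratifying on one centre is simply blocked randomisation. It needs no adjustment and has no bearing on precision.

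**Conclusion.** The concern holds for the continuous secondary outcomes only, as a minor loss of efficiency. With equal SDs and correlations of 0.3 to 0.7, a t-test on change has 1/0.664 = 1.51 down to 1/0.868 = 1.15 times the variance of ANCOVA at 25 per arm. The true size cannot be fixed from the article. It is larger if follow-up scores are much less spread than baseline scores, and it shrinks towards nothing as rk approaches 1. At worst, ANCOVA costs about 2% in variance. The primary relapse comparison is not called into question. The mismatch between centre stratification and a single hospital is real, but it is a harmless point of wording and separate from the precision issue.

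**What to change.** Before unblinding, and so before the data lock planned for November 2025 (Section 2.2.12):

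- For PASI improvement and the changes in VAS, DLQI and Skindex-16, specify ANCOVA with arm and the baseline value of that outcome. State whether PASI improvement is absolute or percentage.
- Include the same baseline value in the GEE or CLMM models.
- Keep the t-test or Wilcoxon comparison as a sensitivity analysis.
- Keep chi-squared or Fisher as the primary relapse comparison. If an analysis adjusted for baseline PASI is added, label it supportive.
- Separately, reconcile Section 2.2.6 with Section 2.2.1, for example by describing permuted blocks at one centre if that is what was done.

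This changes analysis wording only. It needs no further data or participants, and the statistical price is one degree of freedom per model.

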#### 2.2.12 Trial status

We planned to recruit participants from May 2022, with recruitment expected to be completed in January 2025. The follow-up period will finish in September 2025 and all clinical data will be locked in November 2025. This protocol was submitted before completion of recruitment.

### 2.3 Qualitative study (A semi-structured interview)

#### 2.3.1 Participants

Participants recruited in the randomized controlled trial will be enrolled in this semi-structured interview. Additional informed consent must be obtained prior to participation in this qualitative study.

#### 2.3.2 Data collection

The semi-structured interviews will be conducted individually either in a quiet waiting room or online, and will last between 30 and 60 min. During the interviews, participants will be encouraged to express their attitudes, expectations and experiences regarding the combined therapy of GQHF and Ixekizumab. Additionally, open-ended questions will be used to explore participants preferences and challenges related to this therapeutic regimen. Audio recording of each interview will be made to ensure the data authenticity.

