**Methods and analysis:**

This study employs a mixed-method research (MMR) design, encompassing both quantitative and qualitative studies. The quantitative study consists of a randomized controlled trial involving 50 participants with severe PV, who will be randomly allocated to the intervention group (Ixekizumab plus GQHF) and the control group (Ixekizumab plus GQHF placebo) in a 1:1 ratio. Relapse rate is the primary endpoint. The qualitative study involves semi-structured interviews to concurrently explore the acceptability of the application of Ixekizumab combined with GQHF among the enrolled participants.

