#### 2.2.7 Intervention

Ixekizumab, a kind of humanized monoclonal biomedical treatment targeting IL-17A, has been approved for PV by FDA in the United States (Menter et al., 2019) and in China (Chinese Society of Dermatology, 2021). In addition, Ixekizumab is marketed and frequently utilized in clinical practice. Guben Qushi Huayu Formula (GQHF), a kind of CHM, has demonstrated effective for PV in previous clinical and experimental studies (Chen et al., 2024; Zhang et al., 2024; Chen, 2022; Xiang, 2021). The components of GQHF are presented in Table 1.

**TABLE 1 T1:** Component of Guben Qushi Huayu formula.

Scientific name	Pharmaceutical name	Produced from	Doses (g)
*Astragalus membranaceus* (Fisch.) Bge. [Fabaceae]	*Astragali Radix*	Dry rhizoma	30
*Rehmannia glutinosa Libosch*. [Scrophulariaceae]	*Rehmanniae Radix Praeparata*	Dry rhizoma	15
*Atractylodes macrocephala* Koidz. [Asteraceae]	*Atractylodis Macrocephalae Rhizoma*	Dry rhizoma	15
*Smilax glabra* Roxb. [Liliaceae]	*Smilacis Glabrae Rhizoma*	Dry rhizoma	30
*Paeonia lactiflora* Pall. [Ranunculaceae]	*Paeoniae Radix Rubra*	Dry rhizoma	15
*Curcuma phaeocaulis* Val. [Zingiberaceae]	*Curcumae Rhizoma*	Dry rhizoma	10
*Trionyx sinensis* Wiegmann [Trionychidae]	*Trionycis Carapax*	Tergum	30
*Prunus mume* (Sieb.) Sieb. et Zucc. [Rosaceae]	*Mume Fructus*	Fruit	15
*Sarcandra glabra* (Thunb.) Nakai [Chloranthaceae]	*Sarcandrae Planta*	Herbal	15

The intervention group will be administered GQHF granule (Jiangyin, Jiangsu Province, China) after meals twice daily for 12 weeks. Simultaneously, Ixekizumab (Taltz) will be subcutaneously injected with initial dose of 160 mg at week 0 followed by 80 mg fortnightly until week 12. A 36-week follow-up will be carried out subsequently to further observe the clinical effect.

The control group will receive GQHF placebo granule (Jiangyin, Jiangsu Province, China) twice daily for 12 weeks, which is identical with GQHF in appearance and taste. Meanwhile, injection of Ixekizumab (Taltz) will be administered according to the same usage and dosage with the treatment group. The 36-week follow-up period will continue later.

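### Acceptability of GQHF plus ixekizumab is to be drawn from interviews open to both arms, so accounts of benefit, tolerability and preference from placebo recipients would be credited to GQHF unless themes are reported by arm

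*Protocol article*

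**What the plan says.** Section 2.1 of the protocol article divides the aims: the randomised trial addresses feasibility of the combination, and the interviews address its acceptability among those enrolled. The abstract (Methods and analysis) describes "semi-structured interviews to concurrently explore the acceptability of the application of Ixekizumab combined with GQHF among the enrolled participants".

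The source of interviewees is given in section 2.3.1: "Participants recruited in the randomized controlled trial will be enrolled in this semi-structured interview". Separate consent is required; no arm is named.

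On content, section 2.3.2 states that "participants will be encouraged to express their attitudes, expectations and experiences regarding the combined therapy of GQHF and Ixekizumab", and adds open questions on preferences and challenges with the regimen.

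On allocation and masking, section 2.2.6 states: "Recruited participants will be randomly allocated to the intervention group and the control group in a 1:1 ratio" and "Participants and researchers will be rigorously blinded to the group allocation". It keeps the blind until data validation and editing are finished, or a serious adverse event occurs. Section 2.2.7 states: "The control group will receive GQHF placebo granule", and describes the placebo as one "which is identical with GQHF in appearance and taste". Both arms receive the same ixekizumab regimen.

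Section 2.3.3 replaces identifying information with pseudonyms. Section 2.3.4 describes line-by-line open coding, a preliminary analysis after each interview that can change the interview guide, and regular team meetings. Neither section mentions allocation.

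**The concern.** The object of the interviews is one specific regimen, GQHF plus ixekizumab, but the people eligible to be interviewed received one of two regimens and do not know which. Someone in the control arm who is asked about experience of the combination will describe placebo granules plus ixekizumab. Section 1 of the article credits ixekizumab with rapid onset and marked efficacy, so control participants may well report benefit and ascribe it to the combination.

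If those accounts are pooled with the intervention arm's, statements about how well GQHF worked, how it was tolerated or whether patients would choose it cannot be traced to GQHF. Acceptability is one of the two headline aims, and the Discussion says the pilot is to provide preliminary data for a larger mixed-method trial. A theme such as good tolerability of the combination could be carried forward on the word of people who never took the herbal formula.

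**Working it through.** The plan gives no figure on this point, so there is none to reproduce. The check sets the sections side by side and then sizes the placebo share.

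**Step 1: who is asked, about what, and what they received**

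| Element | Source | Content |
|---|---|---|
| Target of inference | Abstract; 2.1 | Acceptability of GQHF plus ixekizumab |
| Interviewees | 2.3.1 | Trial participants who consent, no restriction by arm |
| Question | 2.3.2 | Experience of the combination, put to every interviewee |
| Treatment received | 2.2.7 | GQHF plus ixekizumab, or placebo granules plus ixekizumab |
| Knowledge of arm | 2.2.6 | Concealed from participants and researchers |
| Analysis | 2.3.3, 2.3.4 | Pseudonymised transcripts, thematic coding, no arm label described |

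The target matches what was received in one arm only.

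**Step 2: placebo share among those eligible**

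Inputs: total 50 (section 2.2.5, "this study aims to enroll 50 participants for preliminary assessment") and 1:1 allocation (2.2.6).

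Placebo recipients = 50 × 1/2 = 25; share = 25/50 = 50%.

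**Step 3: placebo share among those interviewed**

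The number of interviews is not stated, and section 2.3.3 refers to data saturation. Assume n interviews, with selection unrelated to arm. The placebo count is then hypergeometric (population 50, 25 on placebo), with mean n × 25/50 = n/2.

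| n (assumed) | Expected on placebo | 95% range |
|---|---|---|
| 10 | 5 | 2 to 8 |
| 15 | 7.5 | 4 to 11 |
| 20 | 10 | 7 to 13 |
| 30 | 15 | 12 to 18 |
| 50 | 25 | 25 (fixed) |

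The chance that no placebo recipient is interviewed is C(25,n)/C(50,n). At n = 10 this is about 0.0003, and it is smaller for larger n. Mixing is therefore practically certain at any of these numbers. The split could also be uneven: by symmetry, 10 interviews could include as few as 10 − 8 = 2 GQHF recipients within the 95% range, and the blinded team could not see this when judging saturation.

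**Step 4: which topics the mixing affects**

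- Valid from either arm: attitudes, expectations, taste (the placebo is matched on it), and the burden of taking granules twice daily alongside injections.
- Not valid from the placebo arm as evidence on GQHF: perceived effect, tolerability, and preference based on either.

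**The case against.** Interviewing both arms of a blinded trial is a legitimate design. Much of acceptability concerns the act of taking the regimen, and the matched placebo lets control participants speak to that. This stands, and it limits the problem to the themes that depend on GQHF itself.

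The article is also condensed. It does not say that themes will be pooled; it is silent on arm. Figure 2, the interview flow diagram, is not shown and could contain a restriction. This partly stands: that both arms are interviewed is read from unrestricted wording in sections 2.1 and 2.3.1. But the mismatch does not come from silence alone. The stated population, the stated question and the stated objective do not fit one another, and the article's own section on qualitative analysis does nothing to resolve that.

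Themes could be split after unblinding without saying so now. That works only if each transcript remains linkable to the randomisation code, and section 2.3.3 mentions pseudonyms but no link.

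A reader might go further and infer that the interviews threaten the blind or contaminate VAS, DLQI, Skindex-16 or PASI, and should therefore be held after the last visit. The document does not support this. No section gives an interview time point for any participant, and running concurrently can simply mean that the two strands proceed in parallel. Nothing says that interviewers score outcomes or ask for treatment guesses. Postponing interviews to week 48 would also add about 36 weeks of recall after the 12-week treatment and could miss participants who drop out.

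**Conclusion.** The concern holds for perceived effect, tolerability and preference attributed to GQHF. On these, the interviews as described would credit the experience of placebo recipients to the combination. It does not hold for attitudes, expectations, taste or regimen burden, which both arms can report.

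The size is an expected 25 of 50 eligible participants (50%) without GQHF exposure. It would be wrong to read this as half of the interviewees: their number is not given, they must consent separately, and a 50% share is expected only if selection is unrelated to arm. The conclusion assumes that the figure not shown adds no restriction by arm.

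The primary endpoint is unaffected. The change is still worth making, because it decides what the trial can conclude on one of its two main aims.

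**What to change.** Amend sections 2.3.3 and 2.3.4 before unblinding:

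1. Keep a secure link from each pseudonymised transcript to the participant's randomisation code.
2. Complete the coding blind to allocation.
3. After unblinding, state the number interviewed in each arm and report themes by arm.
4. Base GQHF-specific acceptability (perceived effect, tolerability, preference) on the intervention arm, with the placebo arm as contrast. Attitudes, expectations, taste and regimen burden may be reported from both arms together.

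If the link cannot be kept, the minimum is to state that the interviews assess the blinded regimen as received, and to draw no GQHF-specific conclusion from them.

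The cost is a few sentences and a little more analysis, with no extra interviews and no change to their timing. The drawback is that GQHF-specific themes rest on fewer transcripts, about half of those collected in expectation, so saturation on those themes may be less secure and should be described as such.
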